#### Secondary outcomes

Secondary outcome measures include mobility on discharge from hospital as assessed using the Timed Up and Go (TUG) [31,35] and the De Morton Mobility Index (DEMMI) [36-38]. Gait speed will also be measured 6 months postdischarge as a secondary outcome measure. Additional secondary outcomes include function, as measured using the Functional Independence Measure (FIM^TM^) [39], health-related quality of life, as measured by the EuroQol health questionnaire (EQ5D) and the EuroQol Visual Analog Scale (EQ-VAS) [40] and subacute length of stay (LOS). These tests will be administered in accordance with previously published protocols. If a participant is unable to complete the EQ5D or EQ-VAS due to cognitive impairment, a proxy will complete it on their behalf.

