#### Discharge

The second assessment will be completed within 48 hours of discharge. Self-selected gait speed (primary outcome) at this assessment will be the primary endpoint of the study. In addition to the primary and secondary outcome assessments, discharge destination and service referrals on discharge will also be collected. For participants discharged to residential care, the day the treating team determined that they required residential care placement and required paperwork was completed will be used in lieu of actual discharge date for this analysis.

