#### Intervention group: enhanced physical activity

In addition to usual care, participants in the enhanced physical activity intervention group will undertake 1 to 2 sessions of additional physical activities on weekdays, and a further two sessions each weekend throughout their inpatient stay (anticipated average of 19 days, based on data from the participating hospitals). Programs will be individually tailored with the aim of increasing the amount of time participants spent performing mobility exercises, such as standing or walking. Intervention protocol guides, which were trialed in the pilot study, [25] will be specified for participants according to their functional level (summary provided in Table 1; full details provided in trial manual available from authors). Specific targets for activity levels on weekdays and weekends have been set, based on pilot data [19,25]. All sessions will be provided by a physiotherapist or physiotherapy assistant not involved in the provision of usual care to participants. At the end of each intervention session, the physiotherapist or allied health assistant will record the amount of time spent performing each activity in 5-minute increments. No specific program to be completed outside of these sessions will be provided.

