### Risk management and safety monitoring

There is a risk that the intervention may result in an increase in adverse events, although no differences between groups were reported in the pilot study [25]. In the event of a fall or medical event, standard hospital procedures will be followed. Falls during hospital stay, mortality and unplanned re-admissions to an acute service (during rehabilitation or within six months postdischarge) will be recorded on an incident form, monitored by an independent Data Safety and Monitoring Committee and reported to the relevant ethics committees.

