### Statistical analysis

The primary analysis will be conducted on an intention-to-treat basis using data from all randomized participants, although a ‘per protocol’ analysis of the primary outcome will also be reported. Primary outcome values missing due to participants’ death will be imputed as zero. An independent adjudication panel, blinded to group assignment, will review records for participants’ who were discharged to an acute facility as medically unwell. Based on the reasons for transfer, the adjudication panel will determine whether the participant was likely to be able to walk and complete a 6-meter walk test at the time of transfer. If the adjudication panel determines the person was unlikely to be able to walk, the missing value will be imputed as zero. If the adjudication panel determines the person was likely to be able to walk, the last measure will be carried forward. Following that, multiple imputation of other missing primary outcome values will be conducted subject to the satisfaction of relevant missingness assumptions. Baseline data will be examined to ensure that the intervention and control groups are comparable using descriptive statistics with 95% confidence intervals.

All outcomes and analyses have been prospectively categorized as primary, secondary, or tertiary. Differences in both primary and secondary endpoints between the two arms of the study will be tested independently at the 0.05 level of significance. No formal adjustments will be undertaken to constrain the overall type I error associated with the secondary analyses. Their purpose is to supplement evidence from the confirmatory primary analysis to help more fully characterize the treatment effect. Results from the secondary analyses will be interpreted in this context.

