#### Secondary outcomes analyses

Between-group differences in gait speed 6 months postdischarge will be assessed using a one-way ANCOVA model that will include self-selected gait speed at baseline as a covariate;

Between-group differences in TUG on discharge will be assessed using a Cox regression model that will include self-selected gait speed at baseline as a covariate;

Between-group differences in DEMMI score on discharge will be assessed using a one-way ANCOVA model that will include DEMMI score at baseline as a covariate;

Between-group differences in FIM score on discharge will be assessed using a median regression model that will include the FIM score at baseline as a covariate;

Between-group differences in EQ5D score on discharge will be assessed using a median regression model that will include the EQ5D score at baseline as a covariate;

Between-group differences in subacute LOS will be assessed using a median regression model that will include the FIM score at baseline as a covariate.

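### Subacute length of stay has no rule for death or acute transfer, so the planned median regression scores those exits as short stays and favours the arm that has more of them

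*Protocol article*

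**What the plan says.** All references are to the protocol article.

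- **Role of LOS.** Subacute LOS is listed under Secondary outcomes. Statistical analysis tests each secondary endpoint at 0.05 without adjustment, as support for the primary result.
- **Method.** Secondary outcomes analyses: "Between-group differences in subacute LOS will be assessed using a median regression model that will include the FIM score at baseline as a covariate". No rule for deaths or transfers accompanies it.
- **Deaths and transfers.** In Statistical analysis, primary-outcome values missing because of "death will be imputed as zero". For acute transfers, a blinded panel "will review records for participants’ who were discharged to an acute facility as medically unwell" and judges whether the person could have walked. Both rules supply a gait speed; neither touches LOS.
- **Safety recording.** Risk management and safety monitoring acknowledges that the intervention may increase adverse events. It provides that "mortality and unplanned re-admissions to an acute service (during rehabilitation or within six months postdischarge) will be recorded on an incident form".
- **Residential care.** Under Discharge, for people going to residential care, the day on which the need was determined and the paperwork completed "will be used in lieu of actual discharge date for this analysis". The analysis meant is not named.
- **Expected stay.** The section on the intervention group gives an "anticipated average of 19 days, based on data from the participating hospitals". No spread is given.

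**The concern.** Missing-data rules do not help here, because a participant who dies or is transferred on day 4 has a known subacute stay of 4 days. Median regression on observed LOS takes that as a value well below the middle of the distribution.

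The Background counts shorter stay among the improvements found in an earlier review of extra physiotherapy, so a reader will take a shorter median as benefit. The same event can therefore score worst on gait speed (zero for death or for being judged unable to walk) and well on LOS. The events concerned are among those the article monitors as possible harms. If the intervention caused more of them, LOS would move in its favour. If it prevented some, LOS would move against it.

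**Working it through.** **The plan's own figure.** The article states no effect size, spread or power for LOS, so there is no LOS figure to reproduce. The sample size rests on gait speed and does not bear on this point. The total of 198 at 1:1 gives 99 per arm.

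**Inputs**
- From the article: mean stay 19 days.
- Assumed: lognormal stays with median 17 days; a proportion p of participants leaving early by death or acute transfer; underlying stays identical in both arms.
- Implied spread: σ = √(2 ln(19/17)) = 0.472, a coefficient of variation of 0.50.

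**Case A: every early exit falls below the median** (for example, exit times uniform on days 1 to 12). The observed median m solves p + (1 − p)F(m) = 0.5, so F(m) = (0.5 − p)/(1 − p) and m = 17·exp(0.472·z), where z is the normal quantile of F(m).

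| p | F(m) | observed median (days) |
|---|---|---|
| 5% | 0.474 | 16.48 |
| 10% | 0.444 | 15.92 |
| 15% | 0.412 | 15.30 |

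- Intervention 10%, control 15%: 15.92 − 15.30 = +0.6 days.
- Intervention 5%, control 15%: 16.48 − 15.30 = +1.2 days.

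The arm with fewer deaths and transfers appears to stay longer, although underlying stays are the same.

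**Case B: each early exit falls at a uniformly random point of that person's own stay.** Some exits now lie above the median, so the shift is smaller. The medians are 16.64, 16.26 and 15.86 days at 5%, 10% and 15%.

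- 10% against 15%: +0.4 days.
- 5% against 15%: +0.8 days.
- With coefficients of variation of 0.5 and 0.7, a 5-point imbalance moves the median by 0.39 to 0.42 days.

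**Equal rates.** At 5%/5% or 10%/10% the difference is 0.0 days.

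**Against sampling noise** (Case B exits, coefficient of variation 0.6, 99 per arm, simulated unadjusted medians). The standard error of the difference in medians is about 1.6 days. The chance of a significant but false shorter stay on intervention is:

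| Early exits, control / intervention | False shorter stay |
|---|---|
| equal | 2.5% |
| 5% / 10% | 4.5% |
| 10% / 20% | about 7% |
| 5% / 25% | 17.5% |

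**Cancelling a real difference.** If intervention stays are truly 1 day longer, excess exits on intervention must reach about 12 points (Case B) or 8 to 9 points (Case A) before the sign changes. That is about 12, or 8 to 9, extra participants among 99.

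**Exits placed beyond the longest stay.** Now F(m) = 0.5/(1 − p), with medians 17.54, 18.16 and 18.89 days at 5%, 10% and 15%.

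- 10% against 15%: −0.7 days.
- 5% against 15%: −1.3 days.

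The sign now favours the arm with fewer deaths and transfers.

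**Residential-care rule.** Removing an assumed 7 or 14 days of waiting gives 0.0 days at equal placement rates. Placement of 10% on control against 20% on intervention gives about −0.6 or −1.0 days; the reverse imbalance gives the opposite sign.

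**The case against.** **The argument rests on silence.** The article nowhere says that a death counts as a favourable stay, and a rule may exist in the full protocol or analysis plan, which are not shown. It is true that the article does not say so. But it fixes the LOS model, and it states its death and transfer rules for gait speed alone. Scoring these exits as short is what the stated model does unless something is added.

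**The effect is modest.** The shift is zero at equal rates, every rate is assumed, and the article reports no adverse-event difference between groups in the pilot. A 5-point imbalance moves the median by well under half a standard error. Deaths, unplanned acute re-admissions and discharge destination are all recorded, so an imbalance would be visible. This stands, and it limits the weight of the point.

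**The remedy changes the question.** Placing exits beyond the longest stay gives −0.7 and −1.3 days where underlying stays are equal, further from zero than the planned analysis. It measures planned discharge alive, not bed-days. This also stands, and is why both analyses should be shown.

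**Stronger readings that the article does not support**
- *A reader might infer that the residential-care rule is an error.* It is disclosed, applies to both arms and plausibly removes placement waiting time. It distorts the comparison only if placement rates or waits differ by arm. Its one textual weakness is that the analysis is not named.
- *A reader might infer that the bias carries into the cost-effectiveness result.* Health economic analysis draws on hospital costing data and the national medical and pharmaceutical benefit schemes, not on this regression.

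**Conclusion.** The point holds as a weakness in how a secondary outcome is scored. As written, deaths and acute transfers enter LOS as short stays, and an imbalance biases the comparison towards the arm with more of them. The size is about 0.4 days (exits at a random point of the stay) to 0.6 days (exits on days 1 to 12) per 5-point imbalance, and zero at equal rates. This rests on lognormal stays with the article's mean of 19 days and on assumed spread, exit rates and exit times.

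A reader might go further and expect the LOS result to point the wrong way. That is possible but not shown: reversing a true 1-day difference needs an imbalance of roughly 8 to 12 points, and nothing in the article predicts one. LOS is supportive and is not named in the listed hypotheses, so the primary conclusion is unaffected.

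**What to change.** 1. Before unblinding, define an LOS analysis as time to planned discharge alive, with death or transfer to acute care as medically unwell as a competing event. A simpler alternative keeps median regression and places these participants beyond the longest observed stay; the median remains estimable.
2. Report it beside the planned observed-LOS median regression, with the number of deaths and acute transfers in each arm.
3. Keep the residential-care date rule. Under Discharge, say that the analysis meant is LOS, if that is the intention, and give LOS by actual discharge date as a sensitivity analysis only.

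The cost is a coding rule, one added analysis and one sensitivity analysis, from events already recorded and discharge dates the hospitals hold. Sample size and conduct do not change. The small downside is that the added estimand is time to planned discharge and no longer bed-days used, which the planned regression shown beside it still describes.

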#### Exploratory analyses of tertiary endpoints

Between-group differences in the outcomes at 6 months postdischarge will be assessed using appropriate regression models that will include relevant measures at baseline as covariates. The exploratory longitudinal analysis for all outcomes over the period from baseline until 6 months postdischarge will be conducted using a mixed model repeated measures approach subject to the satisfaction of the underlying model assumptions.

### Health economic analysis

Health economic modelling will be undertaken to estimate the potential cost-effectiveness of the intervention arm compared to the control arm. Decision analysis [53] will be used to compare downstream consequences of enhanced physical care and Markov [54] and life-tabling [55] techniques will be applied to model outcomes beyond one year. The main output of interest will be incremental cost-effectiveness ratios in terms of net costs per unit of health gain. Net costs will comprise the costs of the enhanced physical activity program minus costs saved from the reduction in downstream health services utilization. Data on health services utilization will include clinical costing data provided by the hospitals, as well as data from the Australian Medical Benefits Scheme (MBS) and Pharmaceutical Benefits Scheme (PBS). The MBS and PBS are the programs through which clinical services and medications, respectively, are subsidized for Australians. Health gains can be measured in a variety of ways. For the proposed study, in addition to clinical outcomes, we will estimate years of life gained and quality-adjusted life years (QALYs) gained. Both will be enabled by the collection of time-to-outcome data and the latter also by collection of the EuroQoL Quality of Life data. All health economic analyses will be undertaken in accordance with recommended approaches, such as 5% discounting of estimated future costs and health gains. To account for any uncertainty in the data inputs for health economic modelling, sensitivity and uncertainty analyses will be undertaken using Monte Carlo simulation techniques [56].

### Dissemination policy

The results of the trial will be presented in international peer-reviewed journals and presented at conferences. Decisions about publications arising from the data set will be ratified by the Management Committee and all named investigators will be eligible to have authorship on publications arising from the trial. Trial staff will also provide workshops to clinicians to assist the translation of findings to clinical practice.

## Discussion

Loss of mobility is a major determinant of the need for inpatient rehabilitation for older adults [57]. However, there is currently little evidence to guide clinicians in the management for older people admitted to rehabilitation. It is hypothesized that optimizing physical activity will lead to improved mobility outcomes for this population. It has been established that programs designed to increase physical activity during inpatient rehabilitation can be delivered to most older patients, but whether increasing physical activity during hospitalization is efficacious or cost-effective has not been tested. This study will assess both the shorter and longer term (6 months following discharge) functional outcomes and healthcare utilization of participants who undergo a program to increase their physical activity in addition to usual rehabilitation compared to those who only receive usual rehabilitation plus social interaction. The results of this study will inform current rehabilitation practice in Australia and worldwide, and will contribute to the development of clinical practice guidelines.

## Trial status

The trial commenced recruitment on 28 January 2014 and is currently open for recruitment. Recruitment will cease when 198 participants have been randomized. It is anticipated this target will be reached by April 2015.

## Abbreviations

ACTRN: Australian New Zealand Clinical Trials Registry
CONSORT: Consolidated Standards of Reporting Trials
DEMMI: De Morton Mobility Index
EQ5D: Euro QoL Health Questionnaire
EQ-VAS: Euro QoL Visual Analog Scale
FIM: Functional Independence Measure
IQR: interquartile range
LOS: length of stay
NHMRC: National Health and Medical Research Council
QALYs: quality-adjusted life years
RCT: randomized controlled trial
TUG: timed up and go
